| Co-Investigator: | [name], [name], [name], [name], [name], [name] |

SYNOPSIS OF PROTOCOL

| TITLE | Combination therapy of pegylated interferon-alpha-2b, nucleoside/nucleotide analogues (NAs) and GMCSF in NA-experienced chronic hepatitis B patients: A prospective, randomized open-label trial (Anchor study) |
| --- | --- |
| SPONSOR | The Chinese National Thirteenth Five Years Project in Science and Technology (2017ZX10202201) |
| INDICATION | NA-experienced CHB |
| OBJECTIVES | Primary: To compare the efficacy (HBsAg loss) and safety of pegylated interferon alfa-2b therapy plus entecavir (ETV) with or without GMCSF or ETV alone in NA-experienced CHB patients who had sustained HBV DNA suppression by ETV treatment. |
| TIRAL DESIGN | A multi-center, randomized, prospective, open-label Phase IV clinical trial. Patients will be randomized 1:1:1 in the IFN+ETV +GMCSF combination therapy group, IFN+ETV group or ETV group. |
| NUMBER OF PATIENTS | Total N 257 |
| TARGET POPULATION | The subjects who pre-treated by ETV for at least 1 year and achieved HBV DNA ≤10^3^ copies/ml & HBsAg <3000 IU/ml. Patients were excluded if they had previously developed drug resistance to ETV, or received IFN or systemic antiviral therapy within the previous 6 months. Patients were also excluded if they were coinfected with the human immunodeficiency virus, hepatitis C virus or hepatitis D virus or if they had decompensated liver disease (defined as a Child-Pugh Score B or C), pregnancy or lactation, or any other contraindication for IFN therapy |
| LENGTH OF STUDY | 96 weeks treatment  24 weeks follow up |
| DURATION OF STUDY | 42 months after first patient randomized |
| INVESTIGATIONAL PRODUCTS  DOSE/ROUTE/REGIMEN | Group 1: Entecavir 0.5mg once per day; P.O.  Group 2: Entecavir 0.5mg once per day (cessation at week 48); P.O. Pegylated interferon alfa-2b 180ug once per week; S.C.  Group 3: Entecavir 0.5mg once per day (cessation at week 48); P.O. Pegylated interferon alfa-2b 180ug per week; S.C. plus GM-CSF (Teerli, Xiamen Amoytop Biotech Co., Ltd, China) 75 μg once-daily for the first 5 consecutive days each month; S.C. |
| ASSESSMENT OF EFFICACY | Primary Endpoint:  HBsAg loss at Week 96.  Secondary Endpoint:   1. HBsAg seroconversion 2. Proportion of patients who achieve undetectable HBV DNA 3. Quantitative HBsAg measurement 4. HBeAg seroconversion 5. ALT normalization 6. Sustained virologic response at the end of follow-up |

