## Clinical assessments and procedures

A baseline visit will be performed, and for subjects in three groups all baseline assessments and procedures must occur prior to administration of the first dose of study drug. Subjects will subsequently be seen for evaluation at the following timepoints:

During treatment period: Day 1, Week 2, 4, 8, 12, 16, 20, 24, 28, 32, 36, 40, 44, 48, 52, 56, 60, 64, 68, 72, 76, 80, 84, 88, 92 and 96

During follow-up: Week 24 post-treatment

Any subject who discontinues study treatment should return to complete assessments as per the Week 96 visit.

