## Criteria for premature withdrawal

Subjects have the right to withdraw from study treatment at any time for any reason.

In the case that the subject decides to prematurely discontinue study treatment (“refuses treatment”), all efforts will be made to complete and report the observations prior to withdrawal as thoroughly as possible preferably by returning to site to complete assessments as per the Week 96 visit and the Treatment Completion CRF.

If possible, a complete final evaluation at the time of the subject’s withdrawal from the study should be made with an explanation of why the subject is withdrawing from the study. When applicable, subjects should be informed of circumstances under which their participation may be terminated by the investigator without the subject’s consent/assent. The investigator may withdraw subjects from the study in the event of intercurrent illness, AEs, pregnancy, lack of compliance with the study and/or study procedures (e.g., dosing instructions, study visits) or any reason where it is felt by the investigator that further follow-up of the subject is impossible or it is in the best interest of the subject to be terminated from the study. Any administrative or other reasons for withdrawal must be documented and explained to the subject.

If the reason for removal of a subject from the study is an AE, the principal specific event will be recorded on the CRF. The subject should be followed until the AE has resolved, if possible.

An excessive rate of withdrawals can render the study non-interpretable; therefore, unnecessary withdrawal of subjects should be avoided.

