## Statistical methods

### Primary Variables

The primary efficacy parameter is HBsAg loss at end of treatment and 24 weeks after the end of treatment. Subjects with missing values for this parameter will be considered non-responders.

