### Analysis populations: ITT and mITT population

The ITT population shall include all subjects who receive at least one dose of study medication. For the ITT population, subjects will be analyzed according to the groups to which they were randomized.

A modified ITT (mITT) analysis was conducted, excluding patients who failed to meet inclusion criteria at baseline prior to randomization. Any patients including in mITT analysis who withdrew from the study, for whatever reason, was classified as a non-responder.

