### Efficacy Analysis

The primary and secondary efficacy analysis will compare efficacy among three groups.

The descriptive statistics depending on the type of variables will be as follows:

Quantitative variable: size, mean, standard deviation, minimum and maximum.

Qualitative, ordinal variables: frequency and percentage per class.

Response rates for primary and secondary endpoints were assessed by calculating percentages and 95% confidence intervals (CIs) for the ITT and mITT populations. Categorical variables were analyzed by the v2 test or Fisher’s exact test, and continuous variables were analyzed by t test or Wilcoxon test as appropriate. Logarithmic transformation was performed in the case of skewed data. Statistical analyses were conducted by SAS version 9.2.

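### The mITT rule scores anyone who leaves the study as a non-responder even with a measured HBsAg result, so a dropout after Week 96 can overturn an observed Week 96 response

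*Protocol*

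**What the plan says.** Two sentences in the statistical chapter decide who is a non-responder.

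- Protocol 10.2.1, Primary Variables: "Subjects with missing values for this parameter will be considered non-responders". The trigger is a missing HBsAg value. No population is named.
- Protocol 10.2.4, Analysis populations: "Any patients including in mITT analysis who withdrew from the study, for whatever reason, was classified as a non-responder". The trigger is leaving the study. Neither the time of leaving nor the availability of a result matters.

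The endpoint is read twice. Section 10.2.1 says: "The primary efficacy parameter is HBsAg loss at end of treatment and 24 weeks after the end of treatment". The synopsis gives a single time point: "HBsAg loss at Week 96". Table 1 schedules HBsAg at Week 96 and again at Week 120.

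The protocol also seeks results from patients who stop or leave early. Section 7.4 says: "Any subject who discontinues study treatment should return to complete assessments as per the Week 96 visit". Section 7.8 adds: "If possible, a complete final evaluation at the time of the subject’s withdrawal from the study should be made".

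Section 10.2.5 assesses response by "calculating percentages and 95% confidence intervals (CIs) for the ITT and mITT populations" and does not name either population as primary. Section 10.2.6 restates the mITT exclusion but does not reconcile the two scoring rules.

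**The concern.** A responder status at Week 96 should depend on the Week 96 sample. Under the mITT sentence it also depends on whether the patient is still in the study months later. A patient with a valid negative HBsAg result at Week 96 who leaves during follow-up loses that response.

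Two things are at stake. First, a measured value of the primary endpoint is replaced by an imputed failure. Second, ITT and mITT are meant to differ only in who is included. If they also differ in how a patient is scored, a gap between the two rates cannot be attributed to the excluded patients. Few events are expected, so a handful of re-scored patients could be visible in the result.

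**Working it through.** **Step 1. Apply both rules to the possible cases**, with Week 96 and Week 120 scored separately.

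| Patient | Time point | 10.2.1 | 10.2.4 (mITT) |
|---|---|---|---|
| Leaves before Week 96, no Week 96 result | Week 96 | non-responder | non-responder |
| HBsAg-negative at Week 96, leaves before Week 120 | Week 96 | responder | non-responder |
| Same patient | Week 120 | non-responder (missing) | non-responder |
| HBsAg-positive at Week 96, leaves before Week 120 | Week 96 | non-responder | non-responder |

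The rules part only in the second row: a withdrawn patient with a measured negative result. A further case is open. If an early-exit sample taken on the Week 96 schedule (7.4, 7.8) were accepted as the end-of-treatment value, an early leaver who is HBsAg-negative would also be scored in two ways. The protocol does not say whether it is accepted.

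**Step 2. Size per patient.** No figure in the plan addresses this point, so there is none to reproduce. Inputs: 80 to 100 per group (10.2.3); the synopsis total of 257 gives 257/3 ≈ 86. One re-scored responder lowers the arm's rate by 100/n points:

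- n = 80: 1.25
- n = 86: 1.16
- n = 100: 1.00

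**Step 3. Size per arm.** If a share w of measured Week 96 responders later leaves the study, the mITT rate is rate × (1 − w). The protocol gives no dropout rate, so w is an assumption. Rates are taken from both statements of the IFN assumption: 10–20% in Numbers of Patients (section 4), 3–10% in Sample Size (10.2.3).

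| Week 96 rate | w = 5% | w = 10% | w = 20% |
|---|---|---|---|
| 3% | 2.85% | 2.7% | 2.4% |
| 10% | 9.5% | 9.0% | 8.0% |
| 20% | 19% | 18% | 16% |

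**Step 4. Direction.** ETV loss is assumed at 0–3%, which is at most 0.03 × 100 = 3 patients, so there is almost nothing to re-score in Group I. Against ETV, the rule mainly lowers the IFN-arm rates. Between Groups III and II, the difference shifts by (k_II − k_III)/n, where k is the number of re-scored responders in each group. The shift can have either sign. For example, with n = 86, k_II = 2 and k_III = 0 (assumed), it is 2/86 = 2.3 points in favour of III.

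**Step 5. Can one patient matter?** Two-sided Fisher's exact test (one of the tests named in 10.2.5), 86 per arm. A 0.05 threshold is assumed, as the protocol states no alpha.

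- 0 ETV responders: 6 in the IFN arm gives p = 0.029; 5 gives p = 0.059.
- 3 ETV responders: 11 gives p = 0.048; 10 gives p = 0.080.

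These are borderline cases chosen to show sensitivity, not forecasts.

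**The case against.** The strongest defence is that the two sentences express one convention. Withdrawal usually leaves the value missing, counting dropouts as failures is common and conservative, and 10.2.1 does not say that missing values are the sole route to non-response. The mITT sentence could be an additional rule or a loose restatement. This stands in part: the rules agree wherever the value is missing. It does not explain why a patient with a result should be scored as if there were none.

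A second defence concerns the endpoint. Sections 5.1 and 10.2.1 name both end of treatment and 24 weeks later. If loss is required at both, a patient who leaves after Week 96 fails for want of a Week 120 value under either rule. This is correct, and the conflict needs Week 96 to be scored on its own. The synopsis does exactly that.

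Three stronger readings are tempting but not supported:

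- A reader might infer that patients who only stopped study drug are also re-scored, because 7.8 uses the same verb for treatment: "Subjects have the right to withdraw from study treatment at any time for any reason". The mITT sentence, however, is limited to leaving the study.
- A reader might infer a bias from unequal adherence, given 96 weeks of injections in two arms and GM-CSF in one. Those pressures act during treatment, GM-CSF only to Week 48. A patient who leaves then will usually lack a Week 96 value, and both rules agree. The documents give no reason for unequal dropout after Week 96.
- A reader might infer that the rule inflates the benefit over ETV. With so few ETV responders expected, it mainly works the other way.

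**Conclusion.** The point holds in a narrow form. As written, the mITT sentence overrides a measured HBsAg result when the patient later leaves the study, while 10.2.1 imputes failure for missing values, and no section reconciles them. The conclusion assumes that Week 96 is scored as its own time point.

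The effect is confined to withdrawn patients with a measured value, mainly those who leave between Weeks 96 and 120. Each re-scored responder costs an arm 1.0 to 1.25 points. How many there will be cannot be derived from the protocol, and the shares used in the working are assumptions. Against ETV the likely effect is a modest understatement of the IFN arms; for III versus II the direction is open. The fault touches the primary endpoint and is cheap to remove, so it should be corrected, but nothing in the documents shows that it would decide the trial.

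**What to change.** Replace the mITT withdrawal sentence in 10.2.4 with one scoring rule for both ITT and mITT, applied separately at each time point:

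- responder: HBsAg negative on a sample taken within that time point's visit window (Table 1: Week 96 ± 3 days, Week 120 ± 7 days);
- non-responder: HBsAg positive in that window, or no result in that window;
- events after the window do not change the score.

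State that an early-exit sample taken on the Week 96 schedule under 7.4 or 7.8, but outside the Week 96 window, does not count as the Week 96 result. Otherwise an early HBsAg-negative leaver could be entered as a Week 96 responder. If loss at both time points is required for any analysis, derive it from the two scores.

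The cost is wording only, with no new data or visits. The downside is that mITT rates may rise slightly compared with the present rule.

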### Efficacy Analysis

The primary and secondary efficacy analysis will compare efficacy among three groups.

The descriptive statistics depending on the type of variables will be as follows:

Quantitative variable: size, mean, standard deviation, minimum and maximum.

Qualitative, ordinal variables: frequency and percentage per class.

Response rates for primary and secondary endpoints were assessed by calculating percentages and 95% confidence intervals (CIs) for the ITT and mITT populations. Categorical variables were analyzed by the v2 test or Fisher’s exact test, and continuous variables were analyzed by t test or Wilcoxon test as appropriate. Logarithmic transformation was performed in the case of skewed data. Statistical analyses were conducted by SAS version 9.2.

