|  | Histology improvement (option) |
| SAFTY: | Adverse events, vital signs and clinical laboratory parameters. |
| PROCEDURES (SUMMARY) | After signing informed consent and meeting screening parameters, patients are randomized to 1 of 3 treatment groups. patients will be evaluated at Day 1, Week 2, 4, 8, 12, 16, 20, 24, 28, 32, 36, 40, 44, 48, 52, 56, 60, 64, 68, 72, 76, 80, 84, 88, 92, 96, 108 and 120. |
| STATISTICAL ANALYSES:  Population: | Intent-to-treat (patients who receive at least one dose of test drug)  Per-protocol (patients who follow the study protocol and complete the study)  All patients receiving at least one dose of study medication and have a subsequent safety assessment will be considered for analyses of safety. |
| Efficacy: | The descriptive statistics depending on the type of variables will be as follows:  Quantitative variable: size, mean, standard deviation, minimum and maximum.  Qualitative, ordinal variables: frequency and percentage per class.  The percentage and 95% CI are employed to serve the calculation of response rates for the primary endpoint and secondary endpoints. The Chi-square test is used for bivariate variables. |
| Safety: | Adverse events   - Adverse events will be assigned preferred terms and categorized into body systems according to the Medical Dictionary for Drug Regulatory Affairs (MEDDRA) classification of the WHO terminology.   Laboratory Safety Data   - The laboratory data will be analyzed according to the   International Conference on Harmonization (ICH) Guideline for Clinical Safety Data Management: Definitions and Standards for  Expedited Reporting (E2). |

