# 3. Objectives of study

To compare the efficacy and safety of Peg-IFN therapy in combination with ETV with or without GM-CSF in NA-suppressed CHB patients who had HBV DNA<1000 copies/ml and HBsAg<3000 IU/ml.

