## Assignment to treatment groups

All the eligible patients were randomly assigned in a 1:1:1 to one of three groups. We used interactive web response system (IWRS) for computer-generated randomisation sequences with a predefined stratification scheme. Randomisation was stratified by HBeAg (positive or negative) state and gender (male or female) at enrolment. A patient will be enrolled in the study and assigned a patient number after all protocol eligibility requirements have been met. The investigator will use the appropriate patient’s Case Report Form (CRF) and record the patient’s allocated treatment or treatment number in the CRF. It is the investigator’s responsibility to ensure that each patient receives the assigned treatment.

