## Procedures for enrollment of eligible subjects

A subject will be enrolled in the study and assigned a screening number after the subject has given informed consent/assent. Once a subject has fulfilled the entry criteria they may be randomized or assigned, as applicable.

The subject randomization numbers will be generated by SAS PROC PLAN with a block size of 6 and were communicated to the sites in sealed envelopes prepared by the statistician based on the randomization sequence. The investigator or designee will use the CRF with the assigned subject number and enter the corresponding number for allocation to the study groups in the appropriate place on each subject’s CRF.

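### The efficacy analysis fixes neither the Group III versus II contrast nor any error control across three arms, and its named tests leave out the randomisation strata and baseline HBsAg

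*Protocol*

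**What the plan says.** All references are to the Protocol.

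- **Comparison.** *Efficacy Analysis*: "The primary and secondary efficacy analysis will compare efficacy among three groups". No pair of groups, testing order, significance level or multiplicity rule is given.
- **Binary endpoints, including HBsAg loss.** *Efficacy Analysis*: "Categorical variables were analyzed by the v2 test or Fisher’s exact test". The first name reads as chi-square, which the Synopsis confirms: "The Chi-square test is used for bivariate variables". Neither is a stratified test.
- **Continuous endpoints.** *Efficacy Analysis*: "continuous variables were analyzed by t test or Wilcoxon test as appropriate". These are two-group tests, and no baseline adjustment is named. The schedule measures HBsAg at screening and day 0.
- **Objective.** *Objectives of study*: "To compare the efficacy and safety of Peg-IFN therapy in combination with ETV with or without GM-CSF". The Synopsis adds the comparison with ETV alone. *Numbers of Patients* and *Sample Size* both justify 80-100 per group by asking whether the combination with GM-CSF raises HBsAg loss.
- **Randomisation.** *Assignment to treatment groups*: "All the eligible patients were randomly assigned in a 1:1:1 to one of three groups" by a web system, and "Randomisation was stratified by HBeAg (positive or negative) state and gender (male or female) at enrolment". *Procedures for enrollment of eligible subjects* instead describes numbers "generated by SAS PROC PLAN with a block size of 6", sent in sealed envelopes, and mentions no strata.
- **Status of the text.** The section is headed as the complete statistical analysis plan.

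**The concern.** Only Group III versus Group II isolates the effect of adding GM-CSF, and the analysis text never names that contrast. The wording allows two readings, and neither serves the objective.

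- **One global test.** A significant result says that the three rates are not all equal. A low ETV rate can produce that alone, so the trial could report a difference among groups that is silent on GM-CSF.
- **Three pairwise tests.** GM-CSF is then tested, but nothing limits the chance of a false positive across the three tests.

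Under either reading the named tests ignore the factors used to randomise. The continuous tests do not adjust for a baseline value that the trial already collects. Both omissions waste precision where there is little to spare: with 86 per arm, power for 10% versus 20% between Groups II and III is about 45%, and 80% power would need 199 per arm (two-sided 5%, assumed).

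**Working it through.** **Inputs from the protocol.** The Synopsis total is 257, and 257/3 = 85.7, taken as 86 per arm. The planned range is consistent: 3 × 80 = 240 and 3 × 100 = 300. It cannot be reproduced as a power calculation, because no alpha, power or GM-CSF rate is stated. HBsAg loss is assumed to be 0-3% on ETV. For the IFN arm it is 10-20% in *Numbers of Patients* and 3-10% in *Sample Size*. The Background reports 8.5% from the earlier switch study.

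**Assumptions.** Two-sided alpha 5%; all stratum sizes and stratum rates; correlations r.

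**1. Global reading, with GM-CSF adding nothing.** X² = Σ(xᵢ − n·p̄)² / [n·p̄(1 − p̄)], rejecting above 5.99 (2 df). The second column puts the expected counts into the formula. At 1/15/15% these are 0.86, 12.9 and 12.9, with p̄ = 0.1033, so X² = 86 × 0.01307/0.0927 = 12.1. The third column is simulated.

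| True rates I/II/III | X² at expected counts | Global test rejects |
|---|---|---|
| 1/15/15% | 12.1 | 98% |
| 1/10/10% | 7.1 | 78% |
| 3/10/10% | 4.0 | 42% |
| 1/5/5% | 2.6 | 23% |
| 1/3/3% | 1.0 | 9% |

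The direct III versus II test rejects in about 5% of trials at 1/10/10% and 3/10/10%. Every global rejection above that level comes from the ETV arm.

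**2. Pairwise reading, all arms equal.** Three independent tests would give 1 − 0.95³ = 14.3%. The real tests share arms, and simulation gives at least one false positive in 11.9% of trials at a common 8.5% (11.3% at 3%, 12.2% at 10%). If pairwise tests are run only after a significant global test, the figure at 8.5% is about 4.6-4.7%. The closure argument is short. If all three rates are equal, the global test limits error to 5%. If exactly two are equal, only one pairwise null is true, and it is tested at 5%.

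**3. Strata.** Plain chi-square against CMH, two arms of 86, with 43 per HBeAg level. Rates are shown by HBeAg level.

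| Stratum rates | Chi-square | CMH |
|---|---|---|
| Size, 5/20% in both arms | about 4.4% | about 5.0% |
| Size, 2/30% in both arms | 3.2% | 5.0% |
| Power, 5/15% v 12/28% (10 v 20% overall) | 44.9% | 46.7% |
| Power, 3/10% v 8/20% (6.5 v 14% overall) | 37.4% | 37.9% |
| Power, 5/20% v 15/40% | 70.5% | 73.1% |
| Power, 2/30% v 8/55% | 69.8% | 77.3% |

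The last two rows imply overall rates of (15 + 40)/2 = 27.5% and (8 + 55)/2 = 31.5% in the better arm, above any rate in the protocol. A separate set with four near-equal strata gave 57.1% to 61.0% and 47.3% to 55.2%.

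**4. Quantitative HBsAg.** ANCOVA leaves 1 − r² of the variance of the end value: 0.64 at r = 0.6 and 0.36 at r = 0.8, a cut of 36% to 64%. Against change from baseline, with equal variances at the two times, the ratio is (1 − r²)/[2(1 − r)] = (1 + r)/2 = 0.80 to 0.90, a cut of 10% to 20%.

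**The case against.** **The text does not say that one omnibus test is used.** A reader might infer it from the phrase about three groups. The documents do not support that: they only list tests, and the t and Wilcoxon tests are two-group tests, which points towards pairwise use. This stands. The defect is that the contrast and its error control are left open.

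**A reader might infer that the ETV arm guarantees a significant global result.** It does not. The 98% needs IFN rates from the higher of the protocol's two assumptions. Under the lower one the test rejects far less often. What survives is that a significant global result, however often it occurs, does not speak to GM-CSF.

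**Omitting the strata is not a validity failure.** This stands. The plain test is conservative and type I error is not inflated. Large gains appear only at assumed stratum rates beyond the protocol's range. With 0-3% loss on ETV, about 0 to 3 events in 86 patients are spread over four cells, so exact stratified tests may give back part of the gain.

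**The trial calls itself a pilot and proof of concept.** That softens the case for strict familywise control. It does not excuse leaving the GM-CSF contrast unnamed, since that contrast is the stated reason for the sample size.

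**Such details may belong in a separate analysis plan.** In part. But this section presents itself as the complete plan and names specific tests, so the point concerns what it fixes. The baseline adjustment is the weakest element: it affects a secondary endpoint, and *Secondary Endpoint* lists HBsAg decline, which already uses baseline.

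**Conclusion.** The point holds in a limited form. The protocol compares three groups with unstratified and two-sample tests, does not fix Group III versus II as the GM-CSF contrast, and sets no error control.

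- **Global reading:** with no GM-CSF effect the test rejects in 9% to 98% of trials across the ETV and IFN rates tabulated, and the result says nothing specific about GM-CSF.
- **Pairwise reading:** familywise error is about 12%.
- **Strata:** an efficiency matter. The gain is about 1 to 2 points of power at protocol-like rates (0.5 and 1.8 in the two rows shown) and about 7 to 8 points if the strata are strongly prognostic.
- **Baseline HBsAg:** a worthwhile but secondary gain whose size depends on an assumed correlation.

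The first two results rest on 86 per arm and two-sided 5%. The last two also rest on stratum sizes, stratum rates and correlations that the protocol does not give. The change should be made, but the present tests are not invalid.

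**What to change.** 1. Reconcile the two descriptions of randomisation (stratified web system; blocks of 6 in envelopes with no strata mentioned). The analysis should use the factors actually applied.
2. Test HBsAg loss across the three arms with a CMH test stratified by those factors, at two-sided 5%.
3. Only if that is significant, run the three pairwise stratified tests at 5% each. For three arms this is a closed procedure and needs no split of alpha.
4. Name Group III versus Group II as the GM-CSF effect. Report its Mantel-Haenszel risk difference with a 95% CI, whatever the tests show.
5. Where ETV events are sparse, use exact stratified tests or collapse to HBeAg alone. Set that rule in advance.
6. Analyse log10 HBsAg by ANCOVA with baseline log10 HBsAg, HBeAg status and gender.

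**Cost.** Wording and a few lines of code; no new data. It is cheap but not free. The gate costs some power against unadjusted testing: at 1/10/10%, at least one pairwise test is significant in 91.5% of trials, but the global test is significant in only 78.1%, which caps the gated figure. Where GM-CSF does add benefit, the loss can be small: at 1/10/20% the global test rejects in 99.2%, so III versus II loses at most 0.8 points. Exact tests are slightly conservative.

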### Secondary Endpoint

The secondary efficacy parameters include (at end of treatment and 24 weeks after the end of treatment)

1. HBsAg positivity and seroconversion
2. Proportion of patients who achieve undetectable HBV DNA
3. Quantitative HBsAg and it’s decline
4. HBeAg seroconversion
5. ALT normalization

6. Sustained virologic response at the end of follow-up

Histology improvement (option)

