### Secondary Variables

All secondary variables will be determined at end of treatment and 24 weeks after the end of treatment.

1. HBsAg positivity (defined as presence of anti-HBs) and seroconversion (defined as loss of HBsAg and presence of anti-HBs)
2. Proportion of patients who achieve undetectable HBV DNA
3. Quantitative HBsAg measurement
4. HBeAg seroconversion (defined as absence of HBeAg and presence of HBeAb in

HBeAg negative patients)

1. ALT normalization (defined as ALT measure ≤ ULN)
2. Sustained virologic response at the end of follow-up

Histology improvement (option)

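### Quantitative HBsAg is tested by an unadjusted t or Wilcoxon test at two visits, leaving baseline and seven of nine post-baseline measurements unused and with no fitting rule for missing values

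*Protocol*

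**What the plan says.** The Efficacy Analysis section names the method for every continuous endpoint: "continuous variables were analyzed by t test or Wilcoxon test as appropriate". It adds that "Logarithmic transformation was performed in the case of skewed data". No covariate, model or repeated-measures term is mentioned.

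The Secondary Variables section fixes the time points: "All secondary variables will be determined at end of treatment and 24 weeks after the end of treatment". These are Weeks 96 and 120. The endpoint is worded in two ways. The Secondary Endpoint section has "Quantitative HBsAg and it’s decline"; the statistical section and the synopsis list the measurement only.

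Table 1 schedules HBsAg at screening, Day 0 and nine later visits, and its footnote sends quantification to the central laboratory.

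There are two missing-data rules. For HBsAg loss, "Subjects with missing values for this parameter will be considered non-responders". For the modified ITT population, a patient "who withdrew from the study, for whatever reason, was classified as a non-responder". On patients who stop treatment, the Clinical assessments and procedures section says: "Any subject who discontinues study treatment should return to complete assessments as per the Week 96 visit".

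**The concern.** The trial is described as a pilot and proof of concept, with 3-10% HBsAg loss assumed on interferon in the Sample Size section (10-20% under Numbers of Patients) and no rate for the GM-CSF arm. With so few primary events likely, the quantitative HBsAg course will carry much of the evidence on whether GM-CSF adds anything. The fixed method uses that course poorly in four ways:

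- It does not adjust for baseline HBsAg, although entry is limited only from above (below 3000 IU/ml) and baseline is measured in everyone.
- It leaves out the intermediate visits, which say something about patients whose Week 96 value is missing.
- It gives no usable rule for a missing concentration. A non-responder has no HBsAg value.
- It makes the scale depend on the observed data. With an assay range of 0.05-52,000 IU/ml, skewness can be foreseen. Patients who lose HBsAg will presumably sit at or below the assay floor, and nothing says what value they receive.

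**Working it through.** **Visits.** The HBsAg row of Table 1 is marked at Weeks 12, 24, 36, 48, 60, 72, 84, 96 and 120. That is nine post-baseline visits, eight of them up to Week 96. The plan tests two, so 9 - 2 = 7 are unused, as is baseline.

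**Inputs.** The protocol gives no precision figure for quantitative HBsAg, so there is nothing to reproduce. The number per arm (257/3, about 86) cancels from the ratios below. Everything else is assumed:

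- dropout d of 5% or 25%, at random and spread evenly over the eight visits to Week 96;
- covariance of log10 HBsAg either compound symmetry (CS, 0.5-0.9), AR(1) (0.8-0.95 per 12 weeks), or a decline with entry SD 0.6, SD of decline 0.9 and residual SD 0.15, as a straight line or a random walk.

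**Gain from baseline.** Let r be the correlation between baseline and Week 96. Adjusting a completer analysis multiplies the variance of the measured-value comparison by 1 - r². With CS 0.5 this is 1 - 0.25 = 0.75, a 25% cut. With AR(1) 0.9, r = 0.9^8 = 0.430, and the cut is 18.5%. Against an unadjusted test of change, with equal variances at both times, the factor is (1 - r²)/(2(1 - r)) = (1 + r)/2, so the cut is (1 - r)/2.

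**Gain from intermediate visits.** Let C be the covariance of the eight visits given baseline. The expected information is I = sum over visits of (d/8) x (inverse of the block of C seen before dropout) + (1 - d) x C⁻¹. The model variance is the Week 96 element of I⁻¹. The adjusted completer variance is C(96,96)/(1 - d). With AR(1) 0.9 and d = 25%, completers keep 75% of the information and the model keeps 82.1%. The cut is 1 - 0.75/0.821 = 8.7%.

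| Covariance | r | Baseline cut, measured value | Baseline cut, change | Visits cut, d = 5% | Visits cut, d = 25% |
|---|---|---|---|---|---|
| CS 0.5 | 0.50 | 25% | 25% | 0.9% | 4.8% |
| CS 0.7 | 0.70 | 49% | 15% | 1.3% | 6.6% |
| CS 0.9 | 0.90 | 81% | 5% | 1.5% | 8.1% |
| AR(1) 0.8 | 0.17 | 2.8% | 41.6% | 1.0% | 5.6% |
| AR(1) 0.9 | 0.43 | 18.5% | 28.5% | 1.6% | 8.7% |
| AR(1) 0.95 | 0.66 | 44% | 16.8% | 1.9% | 10.4% |
| Straight line | 0.53 | 28.4% | 0.2% | 3.5% | 18.2% |
| Random walk | 0.53 | 28.4% | 0.2% | 2.1% | 11.6% |

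The two parts combine as 1 - (1 - baseline cut)(1 - visits cut). Against the unadjusted test of the measured value, the total runs from 1 - 0.972 x 0.990 = 4% (AR(1) 0.8, d = 5%) to 52% (CS 0.7, d = 25%). CS 0.9, a strong assumption over 96 weeks, gives more than 80%.

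On the measured value, baseline is the larger part in every row, except AR(1) 0.8 at 25% dropout. Against change from baseline it is not always larger: in the last two rows nearly all the gain comes from the visits.

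**Bias.** Two interferon arms were simulated with no true difference, SD 1 log10 and AR(1) 0.9, with completers compared at Week 96:

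- random dropout, even 34% v 15%: about 0;
- dropout depending on HBsAg equally in both arms (28% each): about 0;
- dropout depending on HBsAg at about 37% v 18%: about 0.10-0.13 log10, the sign following the direction of dependence;
- only one arm's dropout depending on HBsAg (40% v 15%): up to 0.26.

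For change from baseline the bias in these settings was at most 0.03, and the likelihood model was within 0.01 throughout. A harsher assumption ties dropout directly to poor decline, with a true difference of -0.30. Complete cases then give -0.42 (dropout 10% v 30%) or -0.21 (30% v 15%), and the all-visit estimate stays at -0.30 to -0.31.

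**The case against.** The strongest reply is that this is one of several secondary endpoints, that comparing two fixed visits is legitimate, and that modelling detail often belongs in a separate SAP. The first two parts stand and limit the weight of the point. The third is weak, because the section is headed as the complete statistical analysis plan and names a test.

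Four stronger readings are tempting, and the protocol does not support them.

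- *Dropout costs a quarter of the information.* That only restates an assumed 25% dropout. The protocol gives no rate; it says "An excessive rate of withdrawals can render the study non-interpretable" and no more. Nor would a repeated-measures model restore all of such a loss. With the CS and AR(1) covariances it keeps 79-84% instead of 75%, which is 15-35% of what was lost. The straight-line case recovers about two thirds, but ETV and GM-CSF both end at Week 48 in the GM-CSF arm, so a smooth course is not assured.
- *The GM-CSF comparison is biased.* Bias needs dropout that is related to HBsAg and differs between the two interferon arms. The open-label design and the expectation that GM-CSF helps compliance make this possible, but do not establish it.
- *Only completers are analysed.* The protocol does not say so, and it asks patients who stop treatment for the Week 96 assessments. Stopping treatment is therefore not in itself a missing value. The reply is incomplete, however, because Criteria for premature withdrawal also asks for a final evaluation at the time of withdrawal. An early value could then be counted as end of treatment.
- *The raw scale will be used, or the best of three tests picked.* The protocol already calls for logs when data are skewed, and nothing suggests selection by p-value. What remains is that scale and test are not fixed in advance.

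**Conclusion.** The point holds as a recommendation on a secondary endpoint. The protocol fixes a method that uses neither baseline nor the intermediate visits, leaves scale and test open, and has no missing-data rule that fits a concentration.

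The size rests wholly on assumed dropout and covariance. Against the unadjusted test of the measured value, most of the precision gain comes from baseline adjustment in nearly all settings tried. The part tied to dropout, rounded outwards, is about 1-4% of variance at 5% dropout and about 5-19% at 25%. Bias in the GM-CSF contrast is possible in either direction under the two conditions given, and near zero otherwise. The primary HBsAg-loss analysis has its own missing-data rule and is untouched.

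**What to change.** Replace the general sentence, for quantitative HBsAg, by one pre-specified analysis:

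- Outcome: log10 HBsAg at all scheduled post-baseline visits, whatever the observed skewness. Handle values below 0.05 IU/ml by one stated rule, for example as left-censored.
- Model: likelihood-based repeated measures with arm, visit, arm-by-visit, baseline log10 HBsAg and the stratification factors (HBeAg status and sex).
- Timing: enter each value at its actual visit, so that an early final evaluation is not counted as Week 96.
- Report: arm differences at Weeks 96 and 120 with 95% confidence intervals.
- Sensitivity analysis: Wilcoxon test at Week 96.

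The cost is wording and somewhat more programming, mainly for the censored values. No visits or samples are added. The downside is reliance on missing-at-random, which should be stated.
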